### Description of interventions/comparison groups

The study is a two-group, parallel randomized controlled trial. As such, following the screening visit, eligible participants are randomly assigned to the intervention and control groups in an equal ratio of 1:1. All participants have the smartphone application downloaded free of charge onto their smartphone but not made visible to the user. For the following week after the screening visit (baseline week), all participants are asked to carry their smartphone during walking hours and continue to operate at their normal physical activity levels. All participants are then contacted by SMS and mobile phone at the end of baseline week and asked to Email their baseline step count data to the research team using a ‘share data’ function within the smartphone application.

Once baseline week data collection is completed, those assigned to the intervention group are instructed on how to turn on the smartphone application display (Figure 2) and how to position the display widget on the smartphone home screen. Intervention group participants receive a short instruction by phone on the usability features of the smartphone application settings, feedback graphs (Figure 3), and continuous feedback on their daily step count. Intervention group participants are encouraged to interact with the smartphone application and are encouraged to try to achieve the physical activity goal of 10,000 steps per day. They are also issued with the Irish Heart Foundation ‘Be Active’ physical activity promotion brochure [13] by Email. Intervention group participants are then contacted after two weeks and at the end of the of the follow-up period by SMS and mobile phone, and asked to forward, using a ‘share data’ function within the smartphone application, all daily step count data up to that point. Finally they are instructed to keep their phone charged and to always carry it during walking hours.

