### Outcomes

The primary outcome variable is step count, measured daily for a week prior to treatment assignment (that is, baseline) and subsequently for a seven week follow-up period. Seven secondary outcomes will be measured at baseline and at the end of the follow-up period, namely: systolic blood pressure; diastolic blood pressure; resting heart rate; BMI; mental health as measured by HADS score; quality of life as measured by ED-5D and EQ-VAS. Table 1 outlines the definitions and measurement techniques for each of these secondary outcomes.

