### Analysis plan

Daily step count (primary outcome variable) will be collected longitudinally as described above. All participants will also be invited back for follow-up testing (secondary outcome variables) within one week of finishing the trial. At this follow-up visit, to evaluate the effects of the trial on the secondary outcome measures, data on the same clinical, anthropometric and psychological variables measured at baseline (systolic blood pressure, diastolic blood pressure, resting heart rate, BMI, mental health as measured by HADS score, quality of life as measured by ED-5D and EQ-VAS) will be collected.

Baseline data will be compared across the two arms using suitable numerical summaries and graphical techniques. Functional data analysis techniques, using P-spline smoothers, will be used to graphically represent the eight week daily changes in step count in order to identify a suitable weekly summary statistic.

The effectiveness of the intervention will be assessed using a linear mixed model to compare the change in the primary outcome (within subjects and between treatments) when measured as the mean, median and total weekly steps while adjusting for the following covariates as appropriate: baseline step count, age, gender, socioeconomic status as measured by “medical card eligibility”, BMI, mean systolic blood pressure, mean diastolic blood pressure, mean resting heart rate, mental health as measured by HADS score, quality of life as measured by ED-5D and EQ-VAS and smartphone literacy as measured by whether the participant had activated Email on their smartphone. Those below a certain income level (for example, $238/€184 per week net income for a single person aged up to 65 years who is living alone or $261/€202 per week net income for a single person aged 66 years and over who is living alone) [18] are said to be ‘medical card eligible’ which allows access to family doctor or general practitioner (GP) services, community health services, dental services, prescription medicine costs, hospital care and a range of other benefits free of charge. Therefore, medical card eligibility provides socioeconomic data measured atan individual level. The selection of explanatory variables for inclusion in the final model will be based on a combination of clustering, tree-based methods and variable selection techniques.

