It will be assumed that missing data are missing at random and therefore accounted for in the mixed model. The validity of this assumption will be investigated by looking at the missing data patterns and by modeling the probability of missing data based on the explanatory variables available. The sensitivity of the final conclusions to this assumption will be assessed using multiple imputations via chained equations and predictive mean matching assuming data are missing not at random. Model checking will be performed using suitable model diagnostics and residual plots. All statistical analyses will be performed using the software packages SPSS version 21.0, R version 2.14.3 and Minitab version 16.2.

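### Missing at random does not make days lost inside a partly recorded week accounted for by a mixed model on weekly summaries; the error is largest for an unscaled weekly total

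*Protocol article*

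**What the plan says.** The Outcomes section of the protocol article defines the primary outcome at day level: "step count, measured daily for a week prior to treatment assignment", then for seven weeks of follow-up. In the Analysis plan the daily series is smoothed and plotted "in order to identify a suitable weekly summary statistic". Effectiveness is then assessed with a linear mixed model for the change in the outcome "when measured as the mean, median and total weekly steps". The candidate covariates are baseline steps, demographic, clinical and psychological measures and smartphone literacy. Day of week and number of days recorded are not among them.

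The primary missing-data rule is one sentence: "It will be assumed that missing data are missing at random and therefore accounted for in the mixed model". The plan then inspects missing-data patterns, models the probability of missingness, and adds a sensitivity analysis by "multiple imputations via chained equations and predictive mean matching assuming data are missing not at random". It does not say whether imputation is at day or week level.

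Under Description of interventions/comparison groups, both arms are "instructed to keep their phone charged and to always carry it during walking hours". The application is hidden from everyone in the baseline week; after it, "those assigned to the intervention group are instructed on how to turn on the smartphone application display", and nothing similar is described for controls.

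**The concern.** A likelihood-based mixed model deals with missing values of its own response under missing at random. Here the response is a person-week. A week with no data is a missing response, and the model can handle it. A week with some days recorded yields a number, so the model treats it as observed and cannot see which days are absent. Daily data can be missing at random given arm and day of week while the weekly value is still distorted. The word 'therefore' in the plan's rule then fails even though its assumption is true.

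What is at stake is the between-arm contrast in steps. Recording depends on the phone being charged and carried, and only the intervention arm sees its counts after baseline, so recording could come to differ by arm. Any such difference would arise after the baseline week, so adjusting for baseline steps would not remove it.

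**Working it through.** **Inputs from the protocol article (Sample size and power calculation).** Baseline mean 4,700 steps/day; planned difference 1,410 steps/day; SD of change 2,000; 33 per arm, raised to 40.

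**The plan's own figure.** Normal approximation, two-sided 0.05, 80% power: n = 2 × [2,000 × (1.960 + 0.842) / 1,410]² = 31.6, so 32 per arm. The t-test version gives 32.57, so 33, as stated. Going from 33 to 40 implies 17.5% loss. The sample size is sound and is not affected by this point.

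**Assumptions (not in the documents).** Weekdays are recorded with probability 0.90 in both arms. Weekend days are recorded with probability 0.50 (control) v 0.80 (intervention), or 0.30 v 0.70. Days are independent and the true arm effect is zero. The weekday/weekend gap, where used, is 500 to 1,500 steps.

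**Weekly total, not rescaled, no weekend gap.**
- Planned effect on the weekly scale: 7 × 1,410 = 9,870.
- Cost of one unrecorded day: 4,700 / 9,870 = 48% of that effect.
- 50% v 80%: the arms differ by 2 × (0.80 − 0.50) = 0.6 recorded days a week; 0.6 × 4,700 / 7 = 403 steps/day.
- 30% v 70%: 2 × (0.70 − 0.30) = 0.8 days; 0.8 × 4,700 / 7 = 537 steps/day.

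No weekend pattern in steps is needed. A difference in the number of recorded days is enough.

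**Weekly mean of recorded days.** Bias = gap × (expected weekend share of recorded days, intervention − control). The share is E[B / (A + B)], with A ~ Bin(5, 0.90) and B ~ Bin(2, weekend probability), over weeks with at least one recorded day.

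| Weekend recording, control v intervention | Weekend share, control | Weekend share, intervention | Difference | Bias, gap 500 | Bias, gap 1,500 |
|---|---|---|---|---|---|
| 50% v 80% | 0.170 | 0.259 | 0.088 | 44 (3% of 1,410) | 132 (9%) |
| 30% v 70% | 0.106 | 0.230 | 0.125 | 62 (4%) | 187 (13%) |

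The sign follows the sign of the gap. If either the gap or the difference in shares is zero, the bias is zero.

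**Check by simulation (assumed values).** 40 per arm, eight weeks of daily counts, 60 replicates, true effect zero. Other days were missing 5% of the time. In the first two columns and the last, follow-up weekend days were missing 50% in control v 5% in intervention. Entries are arm contrasts in steps/day; Monte Carlo SEs are 26 to 35.

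| Model | Weekend 1,000 lower | Weekend 1,000 higher | Weekend 1,000 lower, 30% missing in both arms | No gap |
|---|---|---|---|---|
| Weekly mean | −131 | +135 | +36 | +11 |
| Weekly median | −134 | +134 | +50 | −13 |
| Weekly total / 7 | +506 | +722 | +25 | +595 |
| Daily, with day of week | −22 | +11 | +37 | +7 |
| Daily, without day of week | −133 | +125 | +37 | +8 |

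The mean and median are biased only when both conditions hold. The total is biased whenever recording differs by arm. A daily model removes the bias only if it contains the day-of-week term.

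**The case against.** The article condenses a fuller plan. It does not say how a weekly value is formed from fewer than seven days, and a minimum-days rule or weighting may exist elsewhere. That stands: the absence of such a rule is not the point made here. A reader might infer that a week with one or two recorded days enters with the same weight as a full week and that precision is materially lost. The documents do not support this. No section states such a rule, and under the recording rates assumed above weeks with two or fewer recorded days would be only 0.05% to 0.44% of all weeks.

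The plan also does more than assume missing at random: it examines missingness and imputes. Imputing daily counts before summarising would address the problem. But imputation is planned only as a sensitivity analysis and its level is not stated, so the primary estimate stays as it is.

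Both arms get the same carry-and-charge instruction and the same data requests, and the application runs in the background. Failure to share data would lose blocks of weeks, which the weekly model can handle. This is fair: arm-differential recording within weeks is a possibility that the design leaves open, not a documented fact. For the mean and median the bias is also small against sampling error. With SD 2,000 and 40 per arm the SE is 2,000 × √(2/40) = 447, so 44 to 187 steps is about 0.1 to 0.4 SE. This argument does not rescue an unscaled total.

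**Conclusion.** The concern holds in a limited form. The inference from missing at random to being accounted for is right for wholly missing weeks and wrong for days missing inside a partly recorded week, because the response is weekly and the listed covariates carry no day-of-week or recorded-days information.

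The size depends on the summary. For an unscaled weekly total, each unrecorded day costs 48% of the planned weekly effect, and the contrast is off by about 400 to 540 steps/day under the assumed recording splits with no weekend gap. The article does not say whether the total would be rescaled. For the mean and median the bias is about 44 to 187 steps/day (3% to 13% of 1,410), and only if weekend recording differs by arm and weekend steps differ from weekday steps. The documents give no figures for either condition.

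A reader might conclude that all three summaries average the missing days away, or that the trial's contrast is certain to be biased. Neither follows: the total counts missing days as zero, and with equal recording there is no bias in any of the three.

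**What to change.** Make the primary analysis a linear mixed model on the daily counts that participants already share, with unrecorded days left missing. Use fixed effects for arm, study week, day of week and baseline mean daily steps, and random effects for participant and participant-week. Report the between-arm difference in mean daily steps, so the quantity of interest is unchanged. The day-of-week term is the essential part.

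If weekly summaries are kept, either impute at day level before summarising, or use the weekly mean weighted by recorded days and adjusted for the share of weekend days. Do not analyse an unscaled weekly total. Reword the missing-data sentence to say at which level missing at random is assumed.

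The cost is analysis-plan wording, with no new data. The downside is up to 7 × 7 = 49 follow-up rows per participant and a slightly more complex covariance structure.

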### Sample size and power calculation

The sample size required for the proposed RCT is 80 participants. The sample size is based on the following assumptions. Assuming that the mean daily step count at baseline is 4,700 steps, it is estimated that over the length of the trial, the mean step count in the control arm will reduce by 470 (a 10% reduction) and increase by 940 (a 20% improvement) amongst those receiving the intervention [11]. Using a two-sample comparison of the mean improvement between the arms, a sample size of 33 subjects per arm is required to have 80% power at the 0.05 significance level to detect a difference in the mean improvement of 1,410 between the arms, with an estimated standard deviation of the improvement in step count of 2,000. To account for dropouts or loss of patients to follow-up, the sample size will be adjusted upward from 33 to 40 per group. All analyses will be conducted according to the intention-to-treat principle.

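### The missing-not-at-random sensitivity analysis names a procedure that, as described, works under missing at random, so it gives little test of the primary assumption

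*Protocol article*

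**What the plan says.** All of this is in the missing-data paragraph of the protocol article's Analysis plan.

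- **Primary assumption:** "It will be assumed that missing data are missing at random and therefore accounted for in the mixed model".
- **Check on it:** "The validity of this assumption will be investigated by looking at the missing data patterns and by modeling the probability of missing data", using the explanatory variables that are available.
- **Sensitivity analysis:** "The sensitivity of the final conclusions to this assumption will be assessed using multiple imputations". The method is given in full as "multiple imputations via chained equations and predictive mean matching assuming data are missing not at random".

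No shift of imputed values, pattern-mixture or selection model, or reference-group rule is mentioned. The Sample size section raises 33 per arm to 40 to allow for loss. Under Description of interventions/comparison groups, participants in both arms are asked to forward their step data at the end of the baseline week, after two weeks and at the end of follow-up.

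**The concern.** The label and the named method do not match. Predictive mean matching replaces a missing value with an observed value from a participant whose prediction is similar. This treats people with and without data as exchangeable once the observed data are taken into account, which is the assumption the mixed model already makes. Two analyses that share an assumption will usually agree, and their agreement says little about whether the assumption is true.

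The preliminary check has the same limit. A model of missingness on observed variables can show that data are not missing completely at random. It cannot show whether missingness also depends on the unseen step counts.

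At stake is the claim of robustness. Weeks 3 to 7 reach the team only if the participant responds to the final request. Only the intervention arm sees and uses the display, so failure to send data could relate to unseen activity differently in the two arms. If the text is followed literally, the report could claim robustness to a mechanism that was never examined.

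**Working it through.** **1. The plan's own figures.** From the Sample size section: difference 1,410, SD 2,000, 80% power, 0.05 (taken as two-sided).

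n per arm = 2 × (1.960 + 0.842)² × 2,000² / 1,410² ≈ 31.6, so 32 by the normal approximation. The t-test version gives 32.6, so 33, as stated. Raising 33 to 40 implies a loss of 1 − 33/40 = 17.5%. The plan gives no figure for the missing-data analysis itself.

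**2. What a not-at-random departure does.** Suppose a fraction f of the intervention arm is missing, and their true follow-up steps lie D below what the observed data predict. A missing-at-random analysis then overstates the arm difference by about f × D. D is not in the documents. With f = 17.5%:

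| Assumed D (steps/day) | Approximate bias, 0.175 × D |
|---|---|
| 0 | 0 |
| 500 | 88 |
| 1,000 | 175 |
| 2,000 | 350 |

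**3. Does predictive mean matching reveal it?** This was simulated with 200 trials, 40 per arm and seven weekly values.

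- From the protocol: baseline mean 4,700, changes of −470 and +940, SD 2,000.
- Assumed: baseline SD 2,000; within-person weekly correlation 1,700²/2,000² ≈ 0.72; dropout after week 2.
- At-random scenario: dropout depends on the first two weeks, 18.6% lost.
- Not-at-random scenario: 17.4% lost, with an unseen fall of 2,000 steps/day in intervention-arm dropouts.

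A random-intercept mixed model was compared with sequential predictive mean matching (5 donors, 5 imputations). The same imputations were also analysed with the imputed intervention-arm values shifted down. Mean estimated difference over weeks 3 to 7, in steps/day:

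| Scenario | Full data | Mixed model | Plain matching | Shift −1,000 | Shift −2,000 |
|---|---|---|---|---|---|
| At random | 1,395 | 1,394 | 1,354 | 1,168 | 982 |
| Not at random | 1,082 | 1,421 | 1,396 | 1,226 | 1,055 |

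Monte Carlo standard errors of these means are about 25 to 29.

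- Plain matching minus mixed model: 1,354 − 1,394 = −40 (at random) and about −24 (not at random; 1,396.5 − 1,420.8). The estimate itself varies between trials with an SD of about 370 to 400.
- Bias when not at random: mixed model 1,421 − 1,082 = +339; plain matching 1,396 − 1,082 = +314. Matching keeps 314/339 ≈ 93% of the bias.
- Once a shift is added, the same engine responds. It moves by about 171 (1,396.5 − 1,225.8) and 341 (1,396 − 1,055), close to f × shift = 0.174 × 1,000 = 174 and 0.174 × 2,000 = 348.

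**4. What a shift analysis would show here.** At 17.5% loss, lowering imputed intervention values by 1,410 moves the difference by about 0.175 × 1,410 ≈ 247 steps/day. Lowering both arms equally moves it by (f in intervention − f in control) × shift, which is zero when losses are equal. The intervention-only version is therefore the more searching one.

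**The case against.** The strongest reply is that the text does declare a not-at-random assumption. Chained equations and predictive mean matching only describe how values are drawn, and such draws can carry a shift. The size and grid of a shift are details that a journal article commonly leaves to a fuller plan. This stands to the extent that one cannot conclude the trialists have no departure in mind. A reader might also infer that the named method can never show sensitivity. The documents do not support that, and the shifted results above contradict it. What remains is that the article chose to name the method, and the method as named does not have the property attached to it.

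Three other inferences go too far.

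- **Stopping walking causes missing data.** Under Choice and description of the smartphone application, the app runs in the background without user effort. Someone who walks less, or leaves the phone behind, would be expected to record low counts. That is low or mismeasured activity rather than missing data. Failure to send data remains possible, but no mechanism is documented.
- **The effect will be overstated by a known percentage.** Any such figure comes from an assumed mechanism.
- **Participants with missing covariates will be dropped.** HADS, EQ-5D and the clinical measures are taken at screening. Baseline steps could be missing, but no complete-case rule is stated.

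It is also fair that the plan says the assumption will be investigated, not confirmed, and that examining missingness patterns is ordinary good practice. The objection is only to presenting this as evidence on validity.

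**Conclusion.** The point holds in this form: the sensitivity analysis is labelled missing not at random, but the text gives nothing that departs from missing at random. Run as named, it will closely, though not exactly, track the mixed model and give little or no test of the assumption. The model for missingness does not fill that gap.

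The illustrative bias of about +340 steps/day, roughly 24% of the 1,410 design difference (339/1,410), rests on 17.4% loss after week 2 and an unseen fall of 2,000 steps/day confined to intervention-arm dropouts. With no unseen fall it is zero. The near-agreement of the two analyses depends much less on these choices, because both draw on essentially the same observed information.

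A reader might infer that the primary mixed model is invalid. Nothing here shows that. A missing-at-random mixed model is conventional, and the sample size is unaffected. The defect lies in the claim of robustness.

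**What to change.** Keep the chained-equation and predictive-mean-matching engine and add a departure from missing at random, fixed before outcome data are seen.

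1. Impute as planned, then lower the imputed follow-up steps by a stated range of shifts, for example 0 to 1,410 steps/day (the design difference). Do this in the intervention arm only, then in both arms. For weekly totals multiply by seven (1,410 × 7 = 9,870 steps/week).
2. Report the shift at which the conclusion changes, or state that none in the range changes it.
3. Describe the model for missingness as exploratory, to identify predictors of missingness, and not as a check on the validity of the assumption.
4. Optionally, add an imputation that gives missing intervention participants the control-arm pattern or returns them to their own baseline.

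If a fuller plan already specifies such a shift, one sentence stating it is enough. The cost is plan wording and a few extra analysis runs in software already named, with no change to trial conduct or sample size.
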